## Abstract

**Background:**

Anxiety and affective disorders can be disabling and have a major impact on the ability to work. In Denmark, people with a mental disorder, and mainly non-psychotic disorders, represent a substantial and increasing part of those receiving disability pensions. Previous studies have indicated that Individual Placement and Support (IPS) has a positive effect on employment when provided to people with severe mental illness. This modified IPS intervention is aimed at supporting people with recently diagnosed anxiety or affective disorders in regaining their ability to work and facilitate their return to work or education.

**Aim:**

To investigate whether an early modified IPS intervention has an effect on employment and education when provided to people with recently diagnosed anxiety or affective disorders in a Danish context.

**Methods/Design:**

The trial is a randomised, assessor-blinded, clinical superiority trial of an early modified IPS intervention in addition to treatment-as-usual compared to treatment-as-usual alone for 324 participants diagnosed with an affective disorder or anxiety disorder living in the Capital Region of Denmark. The primary outcome is competitive employment or education at 24 months. Secondary outcomes are days of competitive employment or education, illness symptoms and level of functioning including quality of life at follow-up 12 and 24 months after baseline.

**Discussion:**

If the modified IPS intervention is shown to be superior to treatment-as-usual, a larger number of disability pensions can probably be avoided and long-term sickness absences reduced, with major benefits to society and patients. This trial will add to the evidence of how best to support people’s return to employment or education after a psychiatric disorder.

**Trial registration:**

NCT01721824

## Background

Anxiety and affective disorders are often associated with functional disability and can have a major impact on the ability to work [1-4]. Through the 1990s, depression alone was responsible for an annual loss of US$ 17 billion due to work absenteeism and a total cost of US$ 43.7 billion (34.8 billion Euro) each year in direct and indirect societal costs in the USA [4]. In Denmark, mental health problems account for a total of 7.3 billion Euro each year in direct and indirect societal costs [5]. Disability pension and long-term sickness absence account for the majority [5,6]. A significant amount of the total sickness absence in Denmark is due to mental illness, and disability pensions are increasingly awarded due to non-psychotic mental illness [6,7]. Hence it is crucial to start initiatives to support patients with mental health problems in retaining or regaining their employment or education.

The Individual Placement and Support (IPS)-modified, early intervention for people with mood and anxiety disorder (IPS-MA) is an individualised supported employment intervention, aiming at supporting people with recently diagnosed anxiety or affective disorders to obtain and sustain competitive employment through mentor support. It was created in 2011, based on the experience of a 1-year pilot study, aspects from the supported employment intervention IPS and findings from the literature. The method has never been investigated in a clinical trial.

A recent systematic review of randomised trials as well as controlled non-randomised cohort studies [8] found an overall lack of evidence concerning vocational rehabilitation for patients with recently diagnosed bipolar disorders, depression or anxiety disorders, but points to three important initiatives to consider: preventive interventions, return-to-work interventions and interventions concerning short- or long-term loss of employment. Preventive interventions have only been investigated for patients with depression or depressive symptoms, and show evidence in favour of individualised interventions [9-11]. Considering return to work interventions, studies suggest that an individual intervention should be combined with work-place interventions in close collaboration with mental health services [4,12,13]. Returning to work when diagnosed with depression, anxiety or bipolar disorders is also affected by personal and social factors; hence, it is important to incorporate interventions supporting these matters.

Today, vocational rehabilitation mainly consists of two different approaches: pre-vocational training, often referred to as the train-and-place model, and supported employment, referred to as place-and-train [14]. With pre-vocational training, people are trained in company internship programmes, sheltered workshops or wage-subsidised jobs before obtaining competitive employment. Supported employment aims at a rapid search for competitive employment, with on-going support after employment. In Denmark pre-vocational training is still standard.

The most intensively studied supported employment intervention is IPS [15,16], where job consultants are integrated in and act in close collaboration with the mental health services. Several randomised trials [14,17-27] have indicated that IPS is more effective in helping patients with severe mental illness obtain and sustain competitive employment compared to traditional pre-vocational training. A meta-analysis [28] of four randomised trials [29-32] found that, after 18 months, 70.4% had obtained competitive employment in the IPS group compared to 24.3% in the control group. In a review including 11 randomised trials comparing IPS to traditional pre-vocational training, 61% of the patients obtained competitive employment in the IPS group versus 23% in the control group [15]. No studies were found investigating the effect of IPS when provided to people with recently diagnosed affective or anxiety disorder. It is recommended that the intervention be modified and accommodated to psychosocial and medical aspects, and thoroughly investigated in order to show an effect when offered to, for instance, patients with recently diagnosed anxiety or affective disorders [16]. Further studies are needed in order to investigate the effect of such interventions, in addition to mental health treatment, on people’s return to work.

Sherpa ran the pilot study, from October 2010 to September 2011 (unpublished data), during which 46 patients with depression, anxiety or a bipolar disorder were referred to Sherpa from two mental health centres in Copenhagen. Two mentors and a career counsellor were employed at the time. Twenty of the participating patients had obtained either employment or education after a median of 4.2 months (range 1 to 8 months).

The above-mentioned findings from the literature, aspects from the IPS, and the experiences from the 1-year pilot study led to the creation of IPS-MA in 2011.

The IPS-MA is an individualised supported employment intervention, considering personal and social factors, as well as career counselling and financial guidance. Focus is on a rapid search for competitive employment or education, and not sheltered workshops or long internship programmes. Since people with affective disorders or anxiety are treated by either their general practitioner, psychiatric private practitioner or in mental health centres in Denmark, it is difficult to integrate IPS-MA with treatment to the same extend as in IPS. According to IPS-MA, mentors must have an assertive approach to mental health carers and social workers, and collaborate with mental health services as well as job centres and municipalities, and thereby help coordinate services provided by these.

This is the first trial comparing the effect of IPS-MA to treatment-as-usual when provided to people with recently diagnosed anxiety or affective disorders. The hypothesis is that more people receiving IPS-MA will return to work or education compared to the control group.

## Methods

### Design

The Sherpa trial is a randomised, assessor-blinded, clinical superiority trial comparing IPS-MA in addition to treatment-as-usual with treatment-as-usual alone in 324 patients recently diagnosed with an affective disorder or an anxiety disorder (Figure 1).

**Figure 1 F1:**
[figure not shown]
Flow chart for participants in the trial.

### Participants

Participants will be recruited from Mental Health Centres and private practising psychiatrists within the Capital Region of Denmark from 1 October 2011 until 31 January 2014. Inpatients as well as outpatients are eligible.

### Inclusion criteria

Participants must be aged 18 to 60 years, diagnosed by the referring psychiatrists according to the International Classification of Diseases 10th edition criteria of affective disorders (F30-39) or anxiety disorders (F40-41), and not have had contact with mental health services for more than 3 years. They must have been employed or enrolled in education at some time during the past 2 years. They must have a pronounced wish to return to either employment or education, but not being ready to do so within the following 3 months, and equal to ‘match group’ 2 or 3. (‘Match groups’ are categories used by the job centres in Denmark [33] to estimate how far people are from the labour market. Match group 2 refers to people who can participate in pre-vocational training or courses, but who would not be able to take an ordinary job and be off social benefits within 3 months. Match group 3 refers to people with problems so severe that they cannot work or participate in pre-vocational training). Participants must have the ability to read and understand Danish, and give informed consent verbally and in writing.

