### Recruitment and randomisation

Eligible patients are informed about Sherpa, given the written information, and subsequently referred to Sherpa by their psychiatrists, nurse or social worker. A Sherpa employee calls the patient to make an appointment for inclusion and baseline interview. The assessor will interview the participants, but a Sherpa mentor will always attend the interview in order to manage the randomisation after the assessor has left and inform the participant about allocation. When a participant is included in the trial, central randomisation is performed when the Sherpa mentor calls the Copenhagen Trial Unit and gives the relevant participant information.

Randomisation is performed according to a computer-generated allocation sequence with a varying block size concealed from the investigators. The randomisation is stratified by a) four diagnoses (F31: Bipolar affective disorder; F30, F32-39: Affective disorders; F40: Phobic anxiety disorders; or F41: Other anxiety disorders), and b) two match groups (match group 2 or 3).

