#### The control group

Participants randomised to the control group will receive ‘treatment-as-usual’ as offered by the job centres in Denmark [35]. Services vary according to match group and the participant’s possibilities for social support. Participants receiving sickness benefits must attend their first meeting in the job centre within 8 weeks of sickness leave. Match group 2 participants attend follow-up interviews every 4 weeks, whereas match group 3 participants attend follow-up interviews every 3 months. Participants on social security will attend job-seeking interviews every 3 months.

Participants under the age of 30 have the right and obligation to participate in pre-vocational training after no more than 13 weeks of unemployment. Pre-vocational training has to last for at least 6 months. Young participants must not be without some sort of pre-vocational training for more than 4 weeks. Participants over the age of 30 have the right and obligation to participate in pre-vocational training after no more than 9 months of unemployment.

After an individual evaluation, job centres can offer certain pre-vocational training services: company internship programmes in public or private companies as well as in sheltered workshops, wage subsidy jobs, skill development and guidance, and mentor support (often offered by a colleague who helps the participant adapt to the new workplace regarding norms and social competences). Participants receiving sickness benefits can be provided with gradual return to employment, assistive tools, a personal assistant or reimbursement of sickness benefits to the employer from the first day of sickness leave [35].

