#### Register-based information

Information on vital status, use of mental health services, both as in- and outpatient, number of days of admission, sickness absence and use of social benefits will be gathered from the DREAM database or the Danish Psychiatric Case Register (DPCR) [53]. DPCR is the patient-registry system used by the mental health services in Denmark; it contains information on all hospital admissions, number and duration, outpatient contacts and deaths.

An overview of all data collected and the source of collection is shown in Table 1.

**Table 1 T1:** Data collection at baseline and follow-up

**Source of collection**	**Assessment**	**Baseline**	**12 months follow-up**	**24 months follow-up**
Interview	Hamilton Depression Scale (HAM-D6)	x	x	x
	Hamilton Anxiety Scale (HAM-A6)	x	x	x
	Bech-Rafaelsen Mania Scale (MAS)	x	x	x
	Personal and Social Perfomance scale (PSP)	x	x	x
	Global Assessment of Functioning (GAF)	x	x	x
	Suicidal ideation	x	x	x
Self report	Sheehan Disability Scale (SDS)	x	x	x
	Quality of life (WHO-5)	x	x	x
	Empowerment Scale	x	x	x
	Changes Questionnaire	x	x	x
	Client Satisfaction Questionnaire (CSQ)	x	x	x
	Health-related quality of life EQ-5D (EuroQol)	x	x	x
Hospital records	Number of hospital admissions		x	x
	Length of hospital admissions		x	x
	Use of outpatient services		x	x
	Death (all causes)		x	x
	Suicide		x	x
Dream/interview	Sociodemographic information	x	x	x
Dream	Labour market affiliation	x	x	x
Dream/interview	Civil status	x	x	x
DPCR	First contact with mental health care	x		
Dream/interview	Children	x	x	x
Dream/interview	Education	x	x	x
Dream/interview	Cohabitation status	x	x	x
DPCR	Use of mental health service		x	x
Dream	Number of sick days		x	x
Dream	Use of social benefits		x	x
Self report	Treatment and use of other service from the social and healthcare sector		x	
Self report	Service provided by Sherpa		x	

DPCR, The Danish Psychiatric Case Register.

All data will be handled in accordance with the Danish Data Protection Agency.

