### Statistical analyses

Data analyses will be based on the intention-to-treat principle, which means that data will be included in the group to which the participant was randomised, regardless of intervention received. Data will be analysed using the IBM SPSS Statistics version 20 for Windows.

To assess homogeneity of the two groups at baseline, demographic data such as age, gender, marital status, education level, support (social benefits, social security and so forth), diagnosis and Match group at baseline will be presented.

Dichotomous outcomes will be analysed using logistic regression. For primary and secondary outcomes, an unadjusted analysis of the effect of the Sherpa method as an add-on to treatment-as-usual versus exclusively treatment-as-usual will be carried out, as well as an analysis adjusted for stratification variables (diagnosis and Match group). Multiple multivariate imputations will be used to impute a distribution of missing values.

Continuous outcomes will be analysed in a mixed model with repeated measurements. This model is based on the assumption that data are missing at random or missing completely at random [60].

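### The adjusted primary analysis leaves out baseline labour-market affiliation, although entry allows people with and without a job or study place and the register variable is collected

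*Protocol article*

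**What the plan says.** **Who may enter.** Under Inclusion criteria, "They must have been employed or enrolled in education at some time during the past 2 years". A current job or study place is neither required nor excluded. The same section adds "They must have a pronounced wish to return to either employment or education, but not being ready to do so within the following 3 months".

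**Both kinds of participant are foreseen.** The section on the control group lists, among the services for people on sickness benefits, "reimbursement of sickness benefits to the employer from the first day of sickness leave", which presupposes an employer. It also states "Participants over the age of 30 have the right and obligation to participate in pre-vocational training after no more than 9 months of unemployment", which presupposes none.

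**Randomisation.** "The randomisation is stratified by a) four diagnoses" and "b) two match groups (match group 2 or 3".

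**Analysis.** Statistical analyses plans logistic regression for dichotomous outcomes. For primary and secondary outcomes there is an unadjusted analysis and "an analysis adjusted for stratification variables (diagnosis and Match group". Baseline support (benefits, social security) is to be presented only to describe the groups.

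**Data.** Table 1, under Register-based information, lists "Labour market affiliation" from DREAM at baseline, 12 and 24 months.

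**The concern.** The primary outcome is labour-market status at 24 months, so labour-market status before randomisation is close to a baseline measurement of it. Going back to a job that is still open and finding a new one after up to 2 years away both count as success, but they are different tasks. The two groups can reasonably be expected to differ in prognosis.

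If they do, leaving the variable out of the logistic model has two costs. The treatment test has somewhat less power than it could have. The estimate also stays exposed to any chance difference between arms in the share of participants who hold a job or study place. Match group is in the model, but it is defined by capacity: whether someone could join pre-vocational training or take an ordinary job within 3 months. It does not record whether a job or study place is still held.

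**Working it through.** **1. The plan's own sample size.** Inputs from Power and sample size: 30% v 45%, 5% type I error (taken as two-sided), 80% power.

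n per arm = [z₀.₉₇₅ √(2p̄(1−p̄)) + z₀.₈₀ √(p₁(1−p₁) + p₂(1−p₂))]² / (p₂−p₁)², with p̄ = 0.375

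= [1.960 × √0.46875 + 0.842 × √0.4575]² / 0.15²
= [1.342 + 0.569]² / 0.0225 ≈ 162.3

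Rounded up this is 163, against 162 stated. With z = 1.282 for 90% power the result is 217, as stated. Power at 162 per arm is 79.9%. The sample size reproduces and is not in dispute.

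**2. Assumed inputs.** The documents do not give the share holding a job or study place at baseline (assumed 20–50%). Nor do they give that variable's odds ratio for the outcome (assumed from 1 upwards).

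**3. Power against a model with no covariates.** 4,000 simulated trials per cell, 324 participants, marginal rates held at 30% and 45%, Wald test of treatment:

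| Odds ratio of affiliation | Without affiliation | With affiliation |
|---|---|---|
| 1 | about 81% | about 81% |
| 2 | 81–82% | 81–82% |
| 3 | about 81% | 82–83% |
| 5 | about 81% | 85–86% |

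The ranges cover shares of 20%, 35% and 50%. The Monte Carlo standard error of one power figure is √(0.81 × 0.19 / 4000) ≈ 0.6 point.

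**4. Power against the model actually planned.** The plan already adjusts for Match group, so the fair comparison is Match group alone v Match group plus affiliation. With an assumed Match-group odds ratio of 2:

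| Odds ratio of affiliation | Gain in power |
|---|---|
| 1 | none |
| 1.5–2 | about 0–1 point |
| 3 | 2–3 points |
| 4–6 | 3–6 points |

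These are rounded. Runs with other assumed correlations between Match group and affiliation can differ by about a point.

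**5. Chance imbalance.** With share q, the standard deviation of the between-arm difference in that share is √(2q(1−q)/162).

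- q = 0.20: √(0.32/162) = 0.044, so 1.96 SD = 8.7 percentage points.
- q = 0.50: √(0.50/162) = 0.056, so 1.96 SD = 10.9 percentage points.

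The shift in the unadjusted risk difference is this imbalance times the control-arm risk difference between those with and without a job or place.

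- Smallest case (q = 0.20, odds ratio 2; control risks 26.9% and 42.4%): 0.087 × 0.155 = 0.013.
- Largest case (q = 0.35, odds ratio 5; control risks 18.0% and 52.3%): 0.104 × 0.343 = 0.036.

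An unlucky but plausible allocation would therefore move the unadjusted estimate by about 1.3 to 3.6 points, against a planned effect of 15.

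**The case against.** The strongest reply is that nothing here is wrong. An unadjusted analysis plus one adjusted for the stratification factors is standard and matches the randomisation. An analysis plan that is not shown could add covariates. This stands, and so the point is an improvement and not the correction of an error. The article does, however, name the covariate set, so it is fair to comment on that set.

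Match group is also described under Inclusion criteria as a measure of distance from the labour market, and eligibility narrows the range further: everyone is in group 2 or 3 and not ready to return within 3 months. This stands in part. Match group is a proxy, but it does not say whether a post is held.

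Four stronger readings are tempting, and the documents do not support them.

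- *The mixed entry biases the comparison.* Central, concealed randomisation rules this out in expectation.
- *The trial is sized with no margin.* Power and sample size calls 324 a minimum and aims for up to 434 (90% power) if possible. Trial status reports 290 randomised with recruitment still open, so the larger number is not assured, but margin was planned.
- *Both kinds of participant are known to be enrolled.* The control-group section describes services that job centres can offer. It shows that both kinds are foreseen, not in what proportion they entered.
- *A complete job-held variable is ready for use.* No section shows that DREAM separates a sick-listed person with an employer from one without.

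**Conclusion.** The point holds as a modest, free improvement. Entry allows people with and without a job or study place, affiliation is collected before randomisation, and the adjusted model omits it. The planned analysis remains valid without it.

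A reader might infer a power gain of 4 points or more by comparing the affiliation-adjusted model with no adjustment at all. That is the wrong comparator, because the plan already adjusts for Match group. Against the planned model, a gain of that size needs an odds ratio of about 4 or more. At odds ratios up to 2 the gain is about a point at most. The imbalance figures likewise describe the unadjusted estimate, and adjustment for Match group would remove part of that shift where the two variables are related. All these sizes rest on an assumed share and odds ratio for affiliation. The power gains over the planned model rest also on an assumed Match-group odds ratio.

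**What to change.** Before unblinding, state that the adjusted logistic model for the primary outcome contains baseline labour-market affiliation beside diagnosis and Match group. Define the variable from what is recorded: the DREAM category at baseline, supplemented by the baseline interview, which collects education and income base. Code it as job or study place held v none where the records allow the distinction. Where they do not, use the DREAM category itself.

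The cost is one line of analysis wording and the work of writing down the coding rule. No new data collection or change in sample size is needed. Fixing the covariate in advance also avoids a post hoc argument should the baseline table show the arms to differ in support status.

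Optionally, report a standardised risk difference from the adjusted model, so that the result sits on the percentage-point scale used for the sample size.
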